### Safety considerations, systems advice

The potential risks and safety considerations related to the use of the the BEACON Caresystem have been considered and include:

#### Inappropriate suggestions for changes in ventilator settings

Inappropriate changes in ventilator settings, if applied, can have serious consequences. The general strategy employed in this protocol has three components:

The BEACON Caresystem only provides advice in the situation where the models can accurately describe all psychological measurements. The ability of BEACON Caresystem to do so is automatically assessed by the system throughout the protocol and failure to do so means that no advice is provided, which is made visible to the user.Maximal limits have been applied to the amount for which each ventilator setting can be changed in a single advice, meaning that inappropriate advice should have a reduced impact. The maximal advice changes for each ventilator setting are given in table 1.The risks of changing each of the ventilator settings have been considered individually. Low values of inspiratory pressure or volume can result in reduction of minute ventilation and increase in PaCO_2_ and consequently a fall in arterial pH. To assess this, CO_2_ is monitored continuously by the BEACON Caresystem using capnography. High values of inspiratory pressure can result in lung damage. Peak inspiratory pressure is monitored continuously by the BEACON Caresystem, and all mechanical ventilators provide alarms at high values. Low values of respiratory frequency have no apparent detriment other than those specified in reduction of volume. High values of respiratory frequency can result in air trapping. The maximum step in respiratory frequency is limited to 3 breaths/min if the current frequency is ≥18 allowing the onset of trapping to be identified clinically.Although there are small long-term risks associated with increasing inspiratory oxygen due to absorption atelectasis or oxygen toxicity, the major acute risk of changes in inspired oxygenation is arterial hypoxaemia. If the current SpO_2_ ≤92%, then the maximum reduction in FiO_2_ is limited to 2%. In addition, pulse oximetry is monitored continuously by the BEACON Caresystem during the study and an alarm sounded if levels are ≤90%.

To encourage use of the system and perform an evaluation where advice is applied, the application of advice is mandatory. As clinical practice is variable and advice is unlikely to be applied in all cases, the application and effects of advice are monitored by the BEACON Caresystem, and can be interrogated to ensure that the proposed changes have been made and that the effects are considered safe in cases of doubt.

#### System malfunction

In the event of system malfunction, the patient enters standard care until the malfunction is detected and corrected by biomedical engineers.

#### Sampling and measurement of ABG values

ABG sampling is part of routine ICU care. Additional ABG sampling may be required by the BEACON Caresystem than those performed in clinical practice. The BEACON Caresystem requirements, estimated from current experience, are expected to be a maximum of 6 per day in the intervention group.

All other measurements used are obtained from non-invasive means including pulse oximetry and measurement of respiratory gas content, flow and pressure.

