#### Arterial blood gas (ABG)/automatic lung parameter estimator (ALPE)

In situations where mathematical model simulations cannot accurately describe continuous measurements, that is, SpO_2_, fraction of end-tidal CO_2_ (FetCO_2_), or in support ventilator modes respiratory frequency or tidal volume, then retuning of the models is required. In this situation, the BEACON Caresystem requests either an ABG, or a short procedure varying FiO_2_ to assess pulmonary gas exchange (ALPE), as described and evaluated previously,^16–20^ and briefly described in the online supplementary material.

10.1136/bmjopen-2020-042145.supp1Supplementary data

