### Primary and secondary outcomes

The primary outcomes include:

Duration of mechanical ventilation to successful extubation defined as the time from the start of mechanical ventilation, defined as either the time of intubation in the ICU, or the time of admission to the ICU following previous intubation for surgery, and until successful extubation, with successful extubation defined as ≥48 hours of unassisted spontaneous breathing after extubation.

Unassisted spontaneous breathing is defined here to include supplementary oxygen and support with high-flow nasal catheters. Patients with non-invasive mask ventilation are considered to be assisted.

The secondary objectives of the trial are to compare the following variables in the standard care group and BEACON Caresystem group:

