Duration of mechanical ventilation to successful extubation following randomisation defined as the time from randomisation and until successful extubation, with successful extubation defined as ≥48 hours of unassisted spontaneous breathing after extubation.Time from control mode to support mode defined as the time following randomisation, from initiation of control modes of ventilation and until initiation of support modes of ventilation.Time from support mode to successful extubation defined as the time following randomisation, from initiation of support modes of ventilation and until successful extubation.Number of changes in ventilator settings per day defined as the daily registered number of changes to ventilator settings from randomisation until successful extubation.Time to first SBT defined as the time from randomisation to the first performed SBT.Time to first successful SBT defined as the time from randomisation to the first successful SBT.Time to first extubation defined as the time from randomisation to the first extubation attempt.Time to first disconnection from mechanical ventilation defined as the time from randomisation to the point at which mechanical ventilation is first discontinued.Percentage of time in control mode ventilation defined as the time from randomisation which is spent in controlled modes of mechanical ventilation in per cent of duration of mechanical ventilation.Percentage of time in support mode ventilation defined as the time from randomisation which is spent in support modes of mechanical ventilation in per cent of duration of mechanical ventilation.Use of sedatives defined as the cumulative use of sedative drugs from randomisation until successful extubation.Use of neuromuscular blockading agents defined as the cumulative use of neuromuscular blockading agents from randomisation until successful extubation.Number of intubation free days defined as the number of days without intubation from randomisation until successful extubation.Number of reintubations defined as the number of reintubations following extubation from randomisation until successful extubation.Number of tracheostomies defined as the number of patients having tracheostomy performed from randomisation until successful extubation or protocol end.Number of patients on prolonged mechanical ventilation defined as the number of patients on mechanical ventilation ongoing for more than 21 days after the start of mechanical ventilation.Number and types of adverse events related to mechanical ventilation defined as the incidence of adverse events directly related to mechanical ventilation.ICU mortality defined as the mortality from randomisation and until death or ICU discharge.Length of stay defined as the duration of ICU admission from the start of mechanical ventilation and until death or ICU discharge.Mobilisation times defined as the time from randomisation until (1) first mobilisation, for example, sitting on the edge of the bed, standing up and marching on the spot and (2) regaining independency, for example, able to drink/eat or comb hair.Daily patient physiological blood gas status defined as daily ABG values of SaO_2_, PaO_2_, PaCO_2_, pH from randomisation until successful extubation.Daily average physiological status defined as daily averages of measured values of oxygenation (SpO_2_), end-tidal CO_2_ fraction (EtCO_2_), ventilation (respiratory rate, tidal volume, anatomical dead space), pulmonary mechanics (airway pressure, respiratory system compliance) and ventilator settings as measured routinely at the bedside.

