
### Statistical considerations

Sample size was determined by a power analysis of duration of mechanical ventilation. Extrapolation of the 2016 ICU admission data from two London-based NHS hospitals provided a sample size of 548 patients over an 18-month period. In these patients, mean total duration of mechanical ventilation measured in days was 7.2, with an SD of 7.0 days. A study population of 137 patients in each randomisation group would allow detection of a 2 day or 30% improvement in the duration of mechanical ventilation in the BEACON Caresystem group assuming a similar improvement in SD, with an α level of 0.05 and power of 0.8. A 2 days or 30% reduction in duration of mechanical ventilation is similar to that used previously.^6^

Primary and secondary outcomes will be measured across the protocol duration and comparison made by independent samples t-test, or appropriate non-parametric testing if not normally distributed. Complementary analysis will be performed using Kaplan-Meier curves.

The study is not sufficiently powered to allow subgroup analysis for the groups specified in the randomisation strategy.

An independent data safety monitoring committee will be established as part of the study, with this committee responsible for defining stopping criteria. Safety data will be looked at after the first 80 patients have been recruited, with an interim analysis performed following 50% recruitment.

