## Safety, ethics and dissemination

### Adverse events

All adverse events will be monitored and documented until the end of study. Adverse events are reported to the trial sponsor according to their standard operating procedure for further investigation. As patients are critically ill, it is expected that unrelated adverse events will occur as part of hospital stay. Adverse events are therefore only defined in relation to changes in mechanical ventilation, for patients allocated to either the control or intervention arms.

Serious adverse events are defined as:Death, suspected to be caused directly by the settings of mechanical ventilation.Adverse events include the following events suspected to be caused directly by the settings of mechanical ventilation:Pneumothorax.Self-extubation.Hypoxaemia (SpO_2_ <90%; PaO_2_ <8.00 kPa).Alkalaemia (pH >7.5).Acidaemia (pH <7.2).

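### Blood-gas adverse events are compared between arms while the device can prompt extra blood gases in the intervention arm, so detection may be higher there with no true difference

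*Protocol article*

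**What the plan says.** All of this is in the protocol article.

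- **Outcome.** Primary and secondary outcomes sets out to "compare the following variables in the standard care group and BEACON Caresystem group". The list includes "Number and types of adverse events related to mechanical ventilation defined as the incidence of adverse events directly related to mechanical ventilation".
- **Analysis.** Statistical considerations plans a "comparison made by independent samples t-test, or appropriate non-parametric testing if not normally distributed". It does not mention the number of blood gases taken.
- **Definitions.** Adverse events opens its list with "Adverse events include the following events suspected to be caused directly by the settings of mechanical ventilation". Five events follow: pneumothorax, self-extubation, hypoxaemia, alkalaemia (pH above 7.5) and acidaemia (pH below 7.2). Hypoxaemia has two limbs: "Hypoxaemia (SpO_2_ <90%; PaO_2_ <8.00 kPa".
- **Sampling.** Sampling and measurement of ABG values says "Additional ABG sampling may be required by the BEACON Caresystem than those performed in clinical practice" and expects at most 6 per day in the intervention group.
- **Trigger.** The ABG/ALPE section, placed under the intervention arm, covers the case where the models cannot describe the continuous measurements. There, "In this situation, the BEACON Caresystem requests either an ABG, or a short procedure varying FiO"2 to assess gas exchange (ALPE).
- **Control arm.** Study procedure switches advice off in controls while the device keeps collecting data. The Discussion says control care will not be standardised.
- **Safety look.** "Safety data will be looked at after the first 80 patients have been recruited", and an independent committee defines the stopping criteria.

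**The concern.** A pH event can be recorded only if a gas is taken. Here the intervention can itself prompt gases, so it can raise the detection of the events used to judge its safety. The prompts also come when model and measurements disagree. Some of the extra gases may therefore be drawn at abnormal moments, which would push in the same direction.

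A second source of difference is attribution. An event counts only if ventilator settings are suspected as the direct cause. The clinical team applies the advice, and the same team treats both arms, so that team knows the allocation. The article describes no blinded attribution. This could move the comparison either way.

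What is at stake is how the adverse-event outcome, and the data given to the safety committee, can be read. Event counts by arm without the number of gases behind them cannot separate harm from closer looking. The primary outcome is not affected.

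**Working it through.** The article states no figure for adverse events, so there is none to reproduce. Its sample-size figure concerns the primary outcome and is not in question. Only its 137 per arm is used here.

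**Inputs from the article.** At most 6 gases per day in the intervention arm; 137 patients per arm; mean ventilation 7.2 days; entry after at least 24 hours of ventilation.

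**Assumptions, not in the article.** Control arm at 2 to 6 gases per day; the intervention arm at its maximum, with 6 taken as a total; 6.2 days of follow-up (7.2 − 1); the same chance p of crossing a threshold on every gas in both arms, from 0.5% to 3%; gases independent.

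**1. Ratio of detected events.** With equal risk per gas, ratio = intervention gases per day / control gases per day.

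**2. Chance of a false difference.** P(at least one event) = 1 − (1 − p)^(gases per day × 6.2). At p = 1%:
- control at 4 per day: 1 − 0.99^24.8 = 0.221
- intervention at 6 per day: 1 − 0.99^37.2 = 0.312

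Power = Φ[(difference − 1.96 × SE0) / SE1], with SE0 from the pooled and SE1 from the separate proportions. With 137 per arm, SE0 = 0.0534 and SE1 = 0.0531, so Φ[(0.091 − 0.105) / 0.0531] = 0.40. A two-proportion test stands in for the article's generic test.

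| Control vs intervention, gases per day | Ratio | Chance of p < 0.05 with no true difference (p = 0.5% to 3%) |
|---|---|---|
| 6 vs 6 | 6/6 = 1.0 | 5% |
| 5 vs 6 | 6/5 = 1.2 | 9% to 21% |
| 4 vs 6 | 6/4 = 1.5 | 24% to 71% |
| 3 vs 6 | 6/3 = 2.0 | 52% to 99% |
| 2 vs 6 | 6/2 = 3.0 | 82% to 100% |

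If the 6 come on top of 4 routine gases, the ratio is 10/4 = 2.5.

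**3. What shrinks the ratio (4 vs 6 per day).**
- *Long episodes.* If an event is an episode of D hours and gases are T hours apart, detection = min(1, D/T), with T = 6 and 4 hours. At D = 4: 1 / (4/6) = 1.5. At D = 6 or more: 1/1 = 1.0.
- *Oximetry.* If a share s of hypoxaemia is caught by SpO2 in both arms, ratio = s + (1 − s) × 1.5, which is 1.25 at s = 0.5 and 1.05 at s = 0.9. This does nothing for pH events.
- *Shorter ventilation.* If the device shortens ventilation by 30%, raw counts scale by 0.7: 0.7 × 1.5 = 1.05. At 5 vs 6 it is 0.7 × 1.2 = 0.84, so an excess could equally be hidden.
- *ALPE and the causality filter.* Some requests are met without a gas, and not every threshold crossing is attributed to settings. The article gives no figures for either.

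**The case against.** The strongest reply is that no excess has been shown. The article says extra gases may be needed, and 6 is an expected maximum. It does not say whether 6 is a total that routine gases can satisfy. If controls already have 6 per day, or if episodes are long, the ratio is 1.0. This stands, and it rules out any claim that the intervention arm will show more events.

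A reader might make four stronger inferences that the document does not support:
- *Requests are switched off in controls.* This is a fair inference from the disabled advice and from where the request procedure is described, but it is not stated outright.
- *Three of the five events depend on a gas.* Only two do. Hypoxaemia also has an SpO2 route, and the device monitors oximetry continuously.
- *Unblinded bedside staff decide attribution.* The article does not say who judges causality, and events go to the sponsor for further investigation. What can be said is that no blinded attribution is described.
- *The trial could be stopped on an artefact.* No event-count rule or between-arm test is stated for the 80-patient look, and the only listed serious adverse event is death.

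It can also be said that rates per gas belong in an analysis plan or committee charter, and that the daily blood-gas outcome already gives a comparison free of the causality filter. Both points carry some weight. However, the event definitions and the request procedure are fixed in this article, and a later plan can allow for unequal sampling but cannot make it equal.

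**Conclusion.** The concern holds as a risk of unequal detection, not as a demonstrated excess. The plan compares events found on blood gases while the intervention can prompt additional gases, with no common schedule stated. The expected direction is more detected pH events, and PaO2 events to a lesser degree, in the intervention arm. Shorter ventilation there could offset or reverse this in raw counts.

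The size cannot be determined from the document. Ratios of 1.0, 1.5 and 2.0 correspond to 6, 4 and 3 control gases per day. They assume 6 gases per day in the intervention arm, equal risk per gas and short episodes. The false-positive chances rest further on the assumed per-gas probability, follow-up and independence, and serve only as illustration. This bears on the interpretation of one secondary safety outcome and of the interim safety data.

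**What to change.** 1. Keep the reported adverse events exactly as defined, and report all of them.
2. Base the between-arm comparison of pH and PaO2 threshold events, whatever their suspected cause, on one equally scheduled gas per ventilated day in both arms. Daily ABG values are already a secondary outcome, but the article does not say which sample is used. Fix that rule in advance, so that a device-prompted gas does not stand in for the scheduled one.
3. Report the number of gases per ventilated day by arm beside the attributed events, and give the committee both at the 80-patient look.
4. Any SpO2-based comparison should exclude ALPE periods, because ALPE varies inspired oxygen and is described only for the intervention arm. It also needs numeric SpO2 to be retained in both arms, which the sponsor should confirm: the outcome list names daily averages, and the Discussion says waveforms cannot all be stored.

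The cost is analysis work, provided that gas times and values are recorded in both arms. Bedside sampling need not change. The downside is that events between scheduled gases drop out of this comparison, though they are still reported.

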### Ethical approval and consent

Study approval was obtained from the regional ethics committee of the HRA, REC reference: 17/LO/0887. IRAS reference: 226 610. The majority of the trial population lack the capacity to consent. Therefore, participant information sheets and advice are requested from a third party acting as a consultee; in most cases, this person will be a personal consultee, who is someone who knows the person lacking capacity and is able to advise the researcher about that person’s wishes and feelings in relation to the project and whether they should join the research. However, where the personal consultee is not available, the researcher may nominate a professional person to assist in determining the participation of a person who lacks capacity. A nominated professional consultee will be appointed by the researcher to provide advice regarding the patient’s suitability to participation in the research. In the event that a personal consultee is identified after the nominated professional consultee advice has been obtained, the above process for personal consultee declaration will be followed. A patient information sheet will be distributed immediately following the patient being identified as eligible for the study. If a surviving patient regains capacity, they will be approached by the research team to obtain their consent to continue in the study. If the patient refuses consent or withdraws, the intervention will be stopped but the regular/expected medical care will still be provided. Without consent, no additional information about the patient will be collected for the purposes of the study. However, to maintain integrity of the randomised trial, all information collected up to that time will still be used and analysed as part of the study.

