### Patient screening

All patients will be screened for eligibility on admission to the ICU by the research team, including research nurses and clinical research fellows. Advice will be obtained from relatives acting as a personal consultee, or consultant acting as nominated professional consultee. Retrospective consent is then obtained from the patient on regaining capacity. The study will run from September 2017 to November 2020.

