#### Mode/sedation

If the BEACON Caresystem detects substantial spontaneous breathing during control ventilator modes, advice is provided to consider changing to support mode. Additionally, if pH falls below a defined value in support mode, advice is provided to consider changing to control mode or modifying sedation. In either situation, the protocol dictates that the bedside nurse consults with the clinician on duty.

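### A patient who refuses consent before 48 hours of unassisted breathing after successful extubation loses the primary outcome, because one rule stops both the intervention and all data collection

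*Protocol article*

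**What the plan says.** Patient screening describes enrolment on the advice of a personal or nominated professional consultee, and adds: "Retrospective consent is then obtained from the patient on regaining capacity". Ethical approval and consent says who is approached: "If a surviving patient regains capacity, they will be approached by the research team to obtain their consent to continue in the study".

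The same section gives refusal or withdrawal two consequences. For treatment: "If the patient refuses consent or withdraws, the intervention will be stopped but the regular/expected medical care will still be provided". For data: "Without consent, no additional information about the patient will be collected for the purposes of the study". It then limits the damage, for the sake of the trial's integrity: "all information collected up to that time will still be used and analysed as part of the study".

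Primary and secondary outcomes defines the primary outcome as the time from start of ventilation to successful extubation, "with successful extubation defined as ≥48 hours of unassisted spontaneous breathing after extubation". Mask ventilation counts as assisted breathing. ICU mortality and ICU length of stay, both secondary outcomes, run to death or ICU discharge.

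Statistical considerations compares the arms by t-test, or by a non-parametric test if the data are not normal, with Kaplan-Meier curves as a complement.

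**The concern.** The request for consent is tied to regaining capacity, and nothing in the article ties it to extubation or to the 48-hour point. A patient can therefore refuse while the primary outcome is still open. Keeping the data already collected does not help in that case, because the defining event has not yet been observed.

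Such a loss would not be random across the trial population. Only survivors who regain capacity can refuse for themselves; patients who die without regaining it cannot be lost this way. If the timing or frequency of refusal also differed by arm, the comparison of mean durations could be biased. Even without that, evaluable patients are lost from a trial sized at 137 per arm with no stated allowance for loss.

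This is a stated collection rule, not an analysis detail that could be left to a statistical analysis plan. Such a plan can say how to handle missing times but cannot restore them.

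**Working it through.** **1. When is the outcome lost?** Setting the consent rule beside the outcome definition:

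| Time of refusal or withdrawal | Primary outcome | Later ICU data |
|---|---|---|
| Still ventilated (including after a failed extubation) | Unobserved | Lost |
| Extubated, fewer than 48 h unassisted | Unobserved | Lost |
| 48 h or more after successful extubation | Complete and kept | ICU mortality and length of stay lost from then on |

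In the first two rows a t-test or rank test cannot use the partial time. In the Kaplan-Meier analysis the patient is censored, possibly informatively.

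**2. The plan's own sample size.** Inputs from Statistical considerations: mean 7.2 days, SD 7.0, a 2-day or 30% reduction with a similar reduction in SD, α 0.05 (two-sided assumed), power 0.8, 137 per arm. The SD in the device arm is 0.7 × 7.0 = 4.9.

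- n per arm = (7.0² + 4.9²)(1.96 + 0.84)² / 2² = 144; power at 137 is 0.782.
- With the average SD of 5.95, n = 139; power at 137 is 0.794.
- With 30% of 7.2 = 2.16 days and SDs 7.0 and 4.9, n = 123; power at 137 is 0.841.

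The stated 137 is thus reproduced closely. The consent rule does not change that calculation; it changes how many of the 137 are evaluable.

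**3. Power if loss is equal in both arms.** Power = Φ(δ / √((7.0² + 4.9²)/n) − 1.96), with n = 137(1 − loss). The loss rates are assumptions.

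| Loss per arm | n per arm | Power, δ = 2.0 | Power, δ = 2.16 |
|---|---|---|---|
| 0% | 137 | 0.782 | 0.841 |
| 2% | 134.3 | 0.774 | 0.834 |
| 5% | 130.2 | 0.761 | 0.822 |
| 10% | 123.3 | 0.739 | 0.802 |

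**4. Bias if loss differs by arm.** Take no true effect, both arms at 7.2 days. If a share d is lost, and those lost would have averaged m days, the mean of the remaining patients is (7.2 − d·m)/(1 − d). The bias is the device-arm value minus the control-arm value. Both d and m are assumptions.

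| m (days) | 5% vs 5% | 5% control, 10% device | 2% control, 10% device |
|---|---|---|---|
| 3 | 0 | +0.25 | +0.38 |
| 4 | 0 | +0.19 | +0.29 |
| 10 | 0 | −0.16 | −0.25 |
| 14 | 0 | −0.40 | −0.62 |

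Example, m = 3, 2% vs 10%: (7.2 − 0.30)/0.90 − (7.2 − 0.06)/0.98 = 7.667 − 7.286 = +0.38 day.

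A positive value makes the device look worse. The sign depends on whether those lost would have had short or long ventilation, and it reverses if the control arm loses more. For unequal loss, the sizes in the table are about 8% to 31% of the 2-day target (0.16/2 to 0.62/2). For scale, the standard error of the difference under the planning SDs is √((7.0² + 4.9²)/137) = 0.73 day.

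**The case against.** **The rule is an ethical condition, not a statistical mistake.** Stopping collection without consent is legitimate, and keeping earlier data limits the harm. This stands. The point is only that declining the intervention and declining all follow-up are not separated. The article separates them elsewhere: under Spontaneous breathing trial (SBT), a reintubated patient has the device deactivated and is still followed to the end of the protocol.

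**A data-only option may exist in consent material that is not shown.** This is possible. The text as published offers none, and if the consent form does, the section should say so.

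**A reader might infer that every refusal loses the primary outcome.** The documents do not support that. A refusal after the 48-hour point leaves it complete. The article also does not say how often capacity returns before extubation, so the share of refusals that matter is unknown.

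**A reader might infer that the device drives the loss.** The system does advise on mode, and if pH falls in support mode "advice is provided to consider changing to control mode or modifying sedation". A secondary outcome is "Use of sedatives defined as the cumulative use of sedative drugs from randomisation until successful extubation". A difference in wakefulness between arms is therefore conceivable. But that advice is not described as lightening sedation, the decision to extubate follows standard practice in both arms, and if waking and weaning both came sooner the endpoint would come sooner too. No difference between arms is stated or shown.

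**The bias figures are assumed.** This is correct. With 10% lost from one arm, none from the other, and those lost averaging 3 days, the shift is 0.10 × (7.2 − 3)/0.90 = 0.47 day; nothing in the article supports such an extreme pattern.

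**Conclusion.** The point holds in a limited form. Refusal or withdrawal before 48 hours of unassisted breathing after successful extubation leaves the primary outcome unobserved, and the article's rule makes this unavoidable even for a patient who objects only to the intervention. Refusals after that point cost later ICU mortality and length-of-stay data but no primary outcome.

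Loss through the patient's own refusal is confined to survivors who regain capacity, so it may be informative. Whether it differs by arm is unknown, and so are the size and direction of any bias. With assumed losses of 2% to 10% per arm, heavier in the device arm, and decliners averaging 3 to 14 days, the bias runs from about −0.6 to +0.4 day. Equal loss of similar patients gives none under the null, and power for a 2-day effect with SDs 7.0 and 4.9 falls from 0.78 to 0.76 at 5% loss. The case for acting is that the loss is avoidable at little cost, not that a bias has been demonstrated.

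**What to change.** Amend Ethical approval and consent, subject to ethics approval, to separate two decisions:

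- A patient who declines the intervention has it stopped, as now, and is asked separately whether routine-record data may still be collected: extubation, reintubation and non-invasive ventilation to the 48-hour point, and ICU outcome.
- All collection stops only if the patient also declines this. Data collected up to then are kept, as now.

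Keep patients who allow continued collection in their randomised arm. Report refusals and withdrawals by arm and by timing relative to the 48-hour point, so that readers can judge whether the loss is unequal.

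The cost is an ethics amendment and one extra choice in the consent material, with no added procedure or visit. Some patients will still refuse all data, so the loss shrinks but does not disappear.
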